## Recruitment procedures

Screening and recruitment will occur at the COVID screening locations. Patients that are evaluated by SESAL clinicians and triaged to HBC will undergo further screening by project staff to assess if they meet project inclusion criteria. Those that (i) are triaged to HBC by SESAL clinicians and (ii) meet the additional project inclusion criteria will be tested for SARS-CoV-2 via rapid antigen test. Those that receive positive test results will be offered enrollment by study staff.

## Home-based care strategies

At the time of enrollment, participants will be assigned to one of the two following home-based care strategies using a block randomization approach, based on day of presentation to the triage center:

- Strategy 1: Study staff will perform daily phone-based assessments using standardized electronic study tools (tablets). Clinical features will be documented on a phone-based patient monitoring form.
- Strategy 2: Study staff will perform daily phone-based assessments using standardized electronic study tools (tablets). Clinical features and oxygen saturation levels will be documented on a phone-based patient monitoring form. Patients will be provided with a portable pulse oximeter for home use ("MIGHTYSAT" manufactured by MASIMO) or other device certified by the US Food and Drug Administration or European CE). Oxygen saturation level will be assessed up to four times per day (morning, midday, evening, plus during the phone-based assessment) by the patient and/or family member and the lowest stable (i.e. without substantial fluctuations) level recorded during a monitoring period of one minute will be recorded and registered. Patients will be provided monitoring sheets to record the times and dates of the oxygen saturation levels.

Study staff performing patient evaluations and monitoring will be doctors or nurses.

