## Project overview

### Rationale

This project is intended to enhance the existing SESAL HBC approach by providing additional resources and monitoring for patients with confirmed COVID-19 that are discharged home after diagnosis. In addition, given limited data on which home-based care strategies most effectively and efficiently minimize poor outcomes, we aim to monitor two discrete home-based care approaches, daily phone calls from nurses to assess the patient's clinical status, with and without the use of pulse oximeters by patients at home. Assignment to home-based care approach will be randomized. Given the primary goal of the project is to reduce morbidity and mortality due to the COVID-19 pandemic, we will not include a control arm.

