### Inclusion and Exclusion Criteria

Inclusion criteria:

- Acute infection with SARS-CoV-2 confirmed by rapid antigen test.
- Patients triaged to HBC by SESAL clinicians according to existing SESAL policies and protocols.
- **45-59 years of age with at least one comorbidity related to increased risk for poor outcomes due to COVID-19 or 60+ years of age.**
- Live or work in the city where the study is being implemented
- Agrees to participate and signs informed consent

Exclusion criteria:

- Negative for SARS-CoV-2 by rapid antigen test
- Patients not triaged to HBC by SESAL clinicians
- Less than 45 years of age, or 45 - 59 years without any comorbid conditions that increase the risk for poor outcomes due to COVID-19
- Does not live or work in the city where the study is being implemented
- Difficulty giving consent to participate due to a medical condition at the time of enrollment

Patients that do not meet all the inclusion criteria above will be excluded from project enrollment.

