## Home-based care kits and strategies

All study participants will receive COVID-19 HBC kits that include soap, face coverings, information sheets on COVID-19 prevention, and other supplies. Half the COVID-19 home kits will include a two-week supply of ABHS. Study participants will be block randomized into ABHS or no ABHS groups according to the day of the week they are tested for COVID-19. Patients assigned to Strategy 2 will be supplied with a portable pulse oximeter and trained on use and measurement by study staff prior to discharge from the triage center. All patients will be asked to return the portable pulse-oximeter when they are discharged from the study. Upon return of the portable pulse-oximeter at the end of the monitoring period, these patients may receive a phone card or similar item of approximately \$10 value to help defray the costs of transportation. Patients who are triaged to HBC but are deemed ineligible for study enrollment may also be provided with an HBC kit if resources are available.

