## Sample size for primary outcome indicators

To calculate the power to detect a difference between two specific groups, we used a two-sided test of independent proportions with the statistical parameters of alpha 0.05, beta 0.2, and power of 0.8. The intervention effect was selected to provide clinically and operationally meaningful outcomes. In addition, the power calculations are based on the following assumptions.

- Likelihood of referral for higher care: According to a study on the use of pulse oximeters to determine referral of COVID-19 patients to a higher level of care, 24.7% of patients required such a referral, in a second study 33% of patients using a pulse oximeter at home and receiving remote COVID-19 management were referred. Given that those studies were conducted prior to the availability of vaccines, and 34% of the Honduran population is vaccinated, we will use a baseline estimate that 20% of patients will be referred for higher care, with a greater proportion referred in the group using pulse oximeters, given additional opportunities to detect the need for referral. The ability to detect a 6% absolute difference between referral rates between arms requires an enrollment of 804 patients per arm for a total enrollment of 1,608 participants.
- Likelihood of hospitalization: The most recent published COVID-19 study in Honduras identified a 25% hospitalization rate in the general population, prior to vaccine availability. We estimate that 10% of all enrolled patients will be hospitalized, taking into account increasing vaccination coverage and the high risk status of the enrolled population. The ability to detect a 5% absolute difference in hospitalization rates between arms requires 946 participants per arm for a total enrollment of 1,892 participants.
- Length of hospitalization: Given an average of 7.7 days hospitalization per admitted patient (SD 10.8), a per arm/strategy sample size of 773 is powered to detect a 20% difference in length of hospitalization between groups for a total enrollment of 1546 participants.
- Pulse oximetry: Given an estimated mean SpO2 of 93% (SD 7%) at the time of evaluation at a higher level of care, a per arm/strategy sample size of 85 is powered to detect an absolute difference between groups of SpO2 of 3%, for a total of 255 patients referred to a higher level of care, for a total enrollment of 850 participants.

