## Data analysis

The primary analysis will provide unadjusted and adjusted differences between arms/strategies based on the covariates listed. We will perform additional subgroups analyses, specifically examining age, sex, comorbidities, baseline clinical features, and timing of the interventions. Qualitative analyses will be conducted by trained researchers using Excel to organize data, given the limited sample sizes. Research analysis will adhere to the Sex and Gender Equity in Research (SAGER) guidelines including reporting representativeness, presenting disaggregated results regardless of positive or negative outcome, withdrawal/attrition rates, and implications of reported gender on study results.

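### Strategy appears to be allocated by day of presentation: the protocol does not state the randomised unit, the arm may be foreseeable before enrolment, and the sample sizes make no allowance for clustering.

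*Protocol*

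**What the plan says.** Three sections of the protocol bear on allocation.

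- Rationale: "Assignment to home-based care approach will be randomized".
- Home-based care strategies: at enrolment, participants are "assigned to one of the two following home-based care strategies using a block randomization approach, based on day of presentation to the triage center".
- Home-based care kits and strategies, for the second factor, alcohol-based hand sanitizer (ABHS): participants are "block randomized into ABHS or no ABHS groups according to the day of the week they are tested for COVID-19".

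None of them names the randomised unit, the source of the sequence, or any concealment.

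On the order of events, Recruitment procedures has patients triaged, screened by project staff and tested. Then: "Those that receive positive test results will be offered enrollment by study staff". Consent is an inclusion criterion: "Agrees to participate and signs informed consent".

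On size, Sample size for primary outcome indicators uses a "two-sided test of independent proportions with the statistical parameters of alpha 0.05, beta 0.2, and power of 0.8". It mentions no design effect, intracluster correlation or number of days. On analysis, Data analysis states: "The primary analysis will provide unadjusted and adjusted differences between arms/strategies based on the covariates listed".

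**The concern.** If one strategy applies to everyone who presents on a given day, two things follow.

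First, the day (or site-day) is the unit that was randomised. Patients seen at the same site on the same day share the triaging clinicians, the site's workload and the phase of the epidemic, so their outcomes may be correlated. A calculation that treats them as independent then overstates power, and a test that ignores the correlation rejects too often.

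Second, the day is already fixed when staff decide whom to approach. With one arm per day, staff know the arm at the latest after that day's first enrolment. With a weekday pattern, they know it indefinitely in advance. The arm cannot be masked, because oximeters are handed out and taught on site. Staff could then approach, or patients accept, differently by arm. That is a bias, and neither a larger sample nor a cluster-robust variance removes it.

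Third, and conditional on the schedules: strategy and ABHS both follow the day, so the two factors may be partly aliased unless their schedules are crossed. The protocol states no crossing.

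**Working it through.** **1. Are the stated sizes those of independent patients?** Inputs are from Sample size for primary outcome indicators: two-sided alpha 0.05 (z = 1.96) and power 0.80 (z = 0.842).

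For two proportions, with p̄ their mean and d their difference:

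n = [1.96·√(2p̄(1−p̄)) + 0.842·√(p1(1−p1) + p2(1−p2))]² / d²

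With continuity correction: n′ = (n/4)·[1 + √(1 + 4/(n·d))]²

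For two means: n = 2·(1.96 + 0.842)²·SD²/Δ²

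| Outcome | Inputs | Recomputed per arm | Stated |
|---|---|---|---|
| Referral | 20% v 26% | n = 771.1, n′ = 804.1 | 804 |
| Mortality | 7.5% v 4.2% (3.3 points lower) | n = 792.8, n′ = 852.3 | 854 |
| Length of stay | SD 10.8, Δ = 0.20 × 7.7 = 1.54 | 772.0 | 773 |
| Arrival SpO2 | SD 7, Δ = 3 | 85.5 | 85 |
| Hospitalisation | 10% v 15% | n = 685.6, n′ = 725.0 | 946 |
| Hospitalisation | 10% v 5% | n = 434.4, n′ = 473.6 | 946 |

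The first four reproduce to within two patients with a design effect of 1, so no clustering allowance is hidden in them. The 946 does not follow from a 10% rate and a 5-point difference. It does match 20% v 15% with continuity correction (n′ = 944.9), again without clustering.

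**2. What would clustering cost?** Design effect DE = 1 + (m − 1)·ICC, where m is the number of patients enrolled per allocation unit and ICC is the intracluster correlation. The documents give neither. Assumed ranges: m = 5 to 20, ICC = 0.01 to 0.05.

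- Lowest: 1 + 4 × 0.01 = 1.04
- Middle (m = 10, ICC = 0.02): 1 + 9 × 0.02 = 1.18
- Highest: 1 + 19 × 0.05 = 1.95

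Power for referral (20% v 26%, no continuity correction) is taken at n/DE per arm. The type I error of a nominal 5% test that ignores clustering is 2·[1 − Φ(1.96/√DE)].

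| DE | Power at 804 per arm | Power at 946 per arm | Type I error |
|---|---|---|---|
| 1 | 81.6% | 87.4% | 5.0% |
| 1.04 | 80.1% | 86.1% | 5.5% |
| 1.18 | 75.0% | 81.5% | 7.1% |
| 1.95 | 53.5% | 60.3% | 16.0% |

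To keep the stated design point for referral, 804 per arm becomes 837 (804 × 1.04 = 836.2), 949 (804 × 1.18 = 948.7) or 1,568 (804 × 1.95 = 1,567.8).

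At 946 per arm, referral keeps 80% power up to DE of about 946/771.1 = 1.23, and mortality up to about 946/792.8 = 1.19.

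**3. Outcomes measured only in a subset.** Length of stay arises only in admitted patients, whom the protocol puts at 10% of those enrolled. At m = 20 that is about 2 per day, so DE is about 1 + 1 × 0.05 = 1.05. Arrival SpO2 arises only in referred patients, about 20%. At m = 20 that is about 4 per day, so DE is about 1 + 3 × 0.05 = 1.15. The 1.95 therefore does not carry over to these outcomes.

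**The case against.** The strongest objection concerns the premise. The strategy sentence does not say that all patients on a day receive the same strategy. Block randomisation based on day can mean patients randomised within blocks defined by day, and the Rationale calls the assignment randomised. The clearer weekday wording governs ABHS, not strategy. On the within-day reading, clustering by allocation falls away, and so does foreknowledge that comes from one arm applying all day. This ambiguity is real, and the point must stay conditional. It does not clear the plan: the same block-randomised term is used for ABHS, where the weekday decides the group, and a protocol has to state its unit of randomisation.

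Three stronger readings are tempting, and the documents do not support them.

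- A reader might infer that the arm is documented as known before consent. It is not. No section says who holds the schedule or when it is revealed, and assignment is placed at enrolment. Foreknowledge is an inference from one arm per day.
- A reader might infer that all planned analyses ignore the day. Data analysis names no day or site term, but it promises adjusted differences and a look at the timing of the interventions. The statistical analysis plan is not shown and may add such terms. Only the sample-size section is explicit.
- A reader might infer that 80% power is certainly lost. At the lower end of the assumed range it is still 80.1% at 804 per arm. If the largest stated size, 946 per arm, is enrolled, referral power stays above 80% until a design effect of about 1.23. Referral proportion is also not among the starred primary indicators.

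One further caution: patients are followed individually at home and referred on differing later days, so presentation day need not produce a large correlation. That argues for the lower part of the range, but the protocol offers nothing to settle it.

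**Conclusion.** The point holds in conditional form. On the natural reading, the day or site-day sets the arm. The protocol then describes a cluster allocation that staff can foresee, and sizes it as if patients were independent. That the sizes contain no clustering allowance is certain for the four that reproduce. The 946 for hospitalisation needs correcting on its own account.

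The size of the loss rests on assumed values. With m = 5 to 20 and ICC = 0.01 to 0.05, it runs from negligible (DE 1.04) to serious (DE 1.95: 53% power for referral at 804 per arm, and 16% type I error if clustering is ignored). It is much smaller for length of stay and arrival SpO2.

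The risk of selective enrolment does not depend on m or the ICC, but it does depend on one arm applying per day. It is the weightier part, because it cannot be corrected once patients are enrolled.

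**What to change.** State the unit of randomisation, how the sequence is generated and how it is concealed. Then take one of two routes.

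**Preferred.** Allocate individual patients after consent from a concealed permuted-block list, stratified by site and loaded on the tablets already used for enrolment. This removes both the clustering by allocation and the advance knowledge that comes from one arm per day. The cost is loading the list and having both kit types on hand every day.

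**Otherwise:**

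- Declare the site-day as the unit.
- Randomise days with a concealed sequence that is not a weekday pattern and is crossed with the ABHS schedule.
- Analyse with the site-day as cluster (cluster-robust variance or a random effect), with terms for site and calendar period.
- Restate power in the sample-size section with a stated and justified m, ICC and design effect for each outcome.

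The analysis and power changes cost only wording and a less favourable power statement. This route reduces foreknowledge but does not remove it, since staff can learn the day's arm from the first enrolment.

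Under either route, correct the hospitalisation size so that it follows from its stated rate and difference.

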## Referral to higher level of care

Patients meeting referral criteria of  $SpO_2 < 92\%$  or other alarm signs will be referred to the nearest COVID triage center or hospital for care by study staff according to existing SESAL guidelines.

## Home-based care kits and strategies

All study participants will receive COVID-19 HBC kits that include soap, face coverings, information sheets on COVID-19 prevention, and other supplies. Half the COVID-19 home kits will include a two-week supply of ABHS. Study participants will be block randomized into ABHS or no ABHS groups according to the day of the week they are tested for COVID-19. Patients assigned to Strategy 2 will be supplied with a portable pulse oximeter and trained on use and measurement by study staff prior to discharge from the triage center. All patients will be asked to return the portable pulse-oximeter when they are discharged from the study. Upon return of the portable pulse-oximeter at the end of the monitoring period, these patients may receive a phone card or similar item of approximately \$10 value to help defray the costs of transportation. Patients who are triaged to HBC but are deemed ineligible for study enrollment may also be provided with an HBC kit if resources are available.

## Discharge from daily clinical monitoring

All patients will receive daily monitoring until they are discharged from the daily monitoring program.

Criteria for discharge are:

1. Ten days post-symptoms onset and 24 hours without fever. Patients meeting these criteria will be discharged from the daily monitoring program. If a patient continues to experience fever more than 10-days post-symptoms onset they will continue to receive daily monitoring until they are fever-free for more than 24 hours.
- OR
2. Patient is hospitalized. Patients that are not hospitalized will continue in the daily monitoring program until criterion #1 is met.

## Data collection and survey tools

### 1. Enrollment questionnaire

All enrolled patients will complete an enrollment questionnaire that will include demographic and clinical information, risk factors, hand hygiene practices and other WASH variables, and socio-behavioral questions.

Questions will include timing and nature of symptoms, and COVID-19 compatible symptoms, if anyone else in the household has had COVID-19 symptoms in the past 30 days, and if so, when they began and how long they lasted. In order to later link patients with COVID testing results and follow-up visits to the CETTE or hospital in a SESAL database, we will also collect the patient's national identification number, but a unique study identification number will also be assigned. The enrollment questionnaire will also assess risk factors of the participant and household members such as which household members leave the house for work or school and if there are any other possible exposures to COVID-19. Specific questions about the WASH component include assessing the participants' knowledge, attitudes, and practices about hand hygiene in the month prior to visiting the triage center. The enrollment questionnaire will assess access to hand hygiene resources in the participants' homes. The estimated time to complete enrollment and questionnaire is 20-25 minutes.

### 2. Daily acute COVID-19 symptom monitoring

Study staff will document clinical features, including oxygen saturation when applicable, and alarm signs or symptoms during each daily follow-up phone call using a standardized form. Data on COVID-19 compatible symptoms among household members will also be collected; gender and age of household members will be recorded but no additional identifiable information will be collected. These questions will allow investigators to assess if other household members were infected or become infected with COVID-19 as a result of likely in-home transmission or community acquired infection. Daily acute COVID-19 symptom monitoring phone calls are estimated to take 10 minutes.

Study subjects will be provided with information on alarm signs and recommendations on when to seek medical attention, to assist in the event that a household member is found to be symptomatic.

### 3. Inpatient chart review

Patients with SpO2 <92% or who otherwise are decompensating will be referred back to the triage centers or to a higher level. In these cases, investigators will abstract data on clinical course and patient outcomes from relevant health facilities. A standard data abstraction form will be completed for study subjects who were hospitalized or received outpatient supplemental oxygen in the COVID screening location. Data

collected will include patients' disposition at admission and discharge, treatment received, and length of stay. Each inpatient chart review is estimated to take two hours, including travel time for study staff.

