### Objectives

- 1) To support and strengthen existing HBC for higher risk COVID-19 patients in Honduras
- 2) To generate operationally relevant data to provide the Honduras SESAL and other health authorities with HBC guidance and protocols.
- 3) To assess the utility and impact of pulse oximetry on outcomes for HBC.
- 4) To evaluate differences in resource utilization by HBC strategy.
- 5) To assess acceptability of different HBC strategies by patients, study staff, and SESAL clinicians staffing triage centers.
- 6) To assess the prevalence of post COVID-19 conditions.
- 7) To assess participant-reported in-home hand hygiene practices before and after receiving HBC kit.
- 8) To assess if participants with access to alcohol-based hand sanitizer (ABHS) practice hand hygiene more frequently.
- 9) To evaluate preferences for different hand hygiene technologies.

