### Activities

- 1) Screening of suspected COVID-19 patients
- 2) Confirmation of COVID-19 using rapid SARS-CoV-2 Antigen testing.
- 3) Enrollment of eligible patients into one of the two HBC strategies.
- 4) Administration of enrollment questionnaire to collect data on demographics, clinical variables, medical history, risk factors, and patient-reported in-home hand hygiene practices.
- 5) Provision of COVID-19 HBC kits to all study participants, with and without alcohol-based hand sanitizer.
- 6) Daily phone-based or clinical monitoring of HBC patients, with referral of patients reporting warning signs, according to the national guidelines, to a higher level of care.
- 7) Chart review of study participants referred to a higher level of care to assess clinical features and outcomes.
- 8) Administration of serial phone-based questionnaires to study participants, including at discharge from HBC daily monitoring, to assess acceptability of HBC strategy, participant-reported in-home hand hygiene practices, and other WASH and socio-behavioral parameters.
- 9) Administration of questionnaires to study staff, triage center staff, and other relevant stakeholders to assess acceptability of various HBC strategies.
- 10) Administration of qualitative interviews to a small subset of patients to understand their hand hygiene practices, with and without ABHS.
- 11) Longitudinal serial phone-based questionnaires to assess incidence and temporal features of COVID-19 compatible symptoms among study participants, with referral for medical evaluation as needed.

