## Indicators

Specific indicators will be used to assess the feasibility, impact and acceptance of the HBC intervention. Primary outcome indicators are designated with “\*”. Although final indicators may be updated and/or modified, the preliminary set of indicators are listed below.

- Feasibility
  - o Proportion that receive the prescribed HBC intervention
  - o Proportion with complete pulse oximetry data, for relevant arm
  - o Proportion lost to follow-up
- Referral to higher level of care
  - o Proportion referred to higher level care due to hypoxia (i.e. SpO2 < 92%)
  - o Proportion referred to higher level care due to alarm symptoms
  - o Proportion referred to higher level care for any other reason
  - o Proportion referred that reach higher level of care within 24 hours
  - o Proportion who successfully complete HBC without requiring referral
  - o Disposition after referral (home, admission, other) \*
  - o SpO2 level upon arrival to higher level of care
  - o Other clinical measures upon arrival to higher level of care
- Impact on patient outcomes:
  - o Duration of hospitalization (days)\*
  - o Duration of ICU and/or ventilator requirement\*
  - o Mortality\*
- Acceptability
  - o Perception of utility/benefit of strategy (study staff/patients)
  - o Perception of ease of implementation of strategy (study staff)
  - o Changes in hand hygiene behavior

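### The chart review section promises abstraction for all referred participants but limits its standard form to those admitted or given oxygen, leaving no named source of arrival SpO2 or disposition for those sent home

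*Protocol*

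**What the plan says.** Four places in the protocol bear on this.

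- **Activities, item 7** plans "Chart review of study participants referred to a higher level of care to assess clinical features and outcomes". It sets no condition on what happened after referral.
- **Data collection and survey tools, item 3 (Inpatient chart review)** first says that patients with SpO2 below 92%, or otherwise decompensating, are referred, and continues: "In these cases, investigators will abstract data on clinical course and patient outcomes from relevant health facilities". The next sentence narrows this: "A standard data abstraction form will be completed for study subjects who were hospitalized or received outpatient supplemental oxygen in the COVID screening location". The contents then listed are disposition at admission and discharge, treatment, and length of stay.
- **Indicators** states that "Primary outcome indicators are designated with" a star. The starred items include "Disposition after referral (home, admission, other", as well as ICU or ventilator duration. "SpO2 level upon arrival to higher level of care" and other clinical measures on arrival are listed without a star.
- **Sample size for primary outcome indicators** nevertheless sizes arrival SpO2 (mean 93%, SD 7%, difference of 3 points, 85 per arm), counting patients referred to a higher level of care.

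**The concern.** The form rule covers fewer people than the sentence before it, than Activity 7, and than the indicators need. The group left out consists of participants who were referred, assessed and sent home without oxygen.

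That group matters in two ways. A referral that ends at home bears directly on Objective 4, "To evaluate differences in resource utilization by HBC strategy". The Background section suggests that oximetry may spare advanced-care resources, while the sample size section expects more referrals in the oximeter arm. Referrals that end at home are where those two expectations meet.

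For arrival SpO2, the presence of a record would depend on admission or oxygen, and both plausibly depend on SpO2 itself. Selecting on the quantity being measured tends to pull the two arm means together.

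**Working it through.** **1. Who gets a form**

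| Source in the protocol | Group covered |
|---|---|
| Activities, item 7 | all referred |
| Inpatient chart review, sentence before the form rule | all referred |
| Inpatient chart review, form rule | hospitalized, or outpatient oxygen |
| Indicators, disposition after referral | all referred, including home |
| Sample size, arrival SpO2 | all referred |

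The form rule is the odd one out.

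**2. Other possible sources**

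- Discharge from daily clinical monitoring: participants who are not hospitalized stay in daily calls. The call form (item 2) is described as clinical features, oxygen saturation when applicable, alarm signs and household symptoms. Disposition after a referral is not named.
- Enrollment questionnaire: the national identity number is collected "In order to later link patients with COVID testing results and follow-up visits to the CETTE or hospital in a SESAL database". The text does not say that this database holds disposition or arrival SpO2.
- Training and Qualifications of Personnel: staff learn to obtain outcomes from patients, families or facilities. This is training, not an instrument.

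Any of these could show that someone went home. None reliably gives a saturation measured at the facility, and Strategy 1 participants are given no study oximeter.

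**3. How many**

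Inputs from the sample size section: 20% referred (baseline), 10% hospitalized, largest stated enrollment 1,892. Assumption: every hospitalized participant was first referred.

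- Referred: 0.20 × 1,892 = 378. Hospitalized: 0.10 × 1,892 = 189. Referred and not admitted: 378 − 189 = 189, half of those referred and 10% of those enrolled.
- With 20% and 26% in the two arms (average 23%): 0.23 × 1,892 = 435 referred, and 435 − 189 = 246 not admitted (57%).
- The share of these given outpatient oxygen is not stated. Assuming 0% to 50%, about 95 to 189 participants have no form at 20% referral, and 123 to 246 at 23%.

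**4. Possible effect on arrival SpO2**

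The plan's figure first: n per arm = 2 × (1.960 + 0.842)² × 7² / 3² = 85.5, which agrees with the stated 85. The inputs are therefore a 3-point difference and SD 7.

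Illustration: arms distributed N(93, 7) and N(96, 7), with forms only for those arriving below a cut-off c. With z = (c − μ)/7, the observed mean is μ − 7 × φ(z)/Φ(z). At c = 92:

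- μ = 93: z = −0.143, φ = 0.3949, Φ = 0.443, mean = 93 − 7 × 0.3949/0.443 = 86.76
- μ = 96: z = −0.571, φ = 0.3388, Φ = 0.284, mean = 96 − 7 × 0.3388/0.284 = 87.64
- difference = 0.88 instead of 3, with 44% and 28% of referred patients contributing.

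Cut-offs of 90 and 94 give 0.74 and 1.05.

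A gradual rule, in which the chance of a form is 1/(1 + exp((SpO2 − 92)/s)), gives 1.3 for s = 2, 1.7 for s = 3 and 2.0 for s = 4. The value of s is my assumption; the protocol gives none. Attenuation appears in each case tried, but its size follows from the assumed rule.

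**The case against.** A reader might infer from the form rule that participants sent home are simply not captured, so that one category of a primary outcome is lost. The protocol does not support that. The sentence immediately before the form rule provides for abstraction in referred cases generally, and lacking a standard form is not the same as lacking data. The starred disposition is the less exposed item: hospitalization ends daily monitoring and everyone else stays in the calls, so admitted versus still at home is largely known from running the study. Identity-number linkage and staff tracing add to that. This stands, although none of these sources is stated to record disposition.

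It is also tempting to say that the form lacks arrival SpO2 and ICU or ventilator days. The listed contents are introduced as what the data will include, so the list need not be complete, and the form itself is not shown. This stands too; it supports naming the fields, not declaring them absent.

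The attenuation figure invites the strongest over-reading. No section makes admission or oxygen depend on arrival SpO2 alone, and referral for other alarm signs allows admission with preserved saturation. The normal model puts about 16% and 28% of the two arms above 100%. If abstraction follows the broader sentence, there is no selection at all. The 0.9 points is therefore a near-worst-case illustration, not an estimate.

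Finally, arrival SpO2 is unstarred and the indicator list is described as preliminary. That lowers the stakes, but the measure still appears in the sample size section for primary outcome indicators.

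**Conclusion.** The point holds as an internal inconsistency. The form rule is narrower than the sentence before it, than Activity 7, and than what the indicators and the SpO2 sample size require. For participants referred and sent home without oxygen, no named instrument is stated to record disposition or arrival SpO2. Disposition can probably be recovered elsewhere; arrival SpO2 probably cannot.

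The group is about 10% of enrolled participants on the protocol's rates, less an unstated share given oxygen, and this assumes that all hospitalized participants were referred. If the form rule is followed literally, the arm difference in arrival SpO2 is probably attenuated. That direction rests on admission or oxygen being related to SpO2, which is plausible but not stated, and the size cannot be determined from the protocol.

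This should be corrected before data collection because facility measurements may be hard to recover later. It does not by itself invalidate a primary outcome.

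**What to change.** In the Inpatient chart review section, complete the abstraction form for every referred participant, whatever the result, so that it agrees with Activity 7 and with the section's own preceding sentence. For those sent home, a short version is enough: date, arrival SpO2, and disposition (home, admission, other). List arrival SpO2 and ICU or ventilator days among the fields so that they match the Indicators section, and retitle the section, since it would no longer concern inpatients only. Daily calls can prompt the short form, with confirmation against the facility record.

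The cost is protocol wording plus modest extra abstraction time for roughly the 10% of participants referred and not admitted. The protocol allows two hours per inpatient review including travel; a short form should need less abstraction, though travel to the facility may remain. No participant visit or procedure is added.
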